## Abstract

**Background**: Upright position recovery (i.e., verticalization) is crucial in the rehabilitation of severe acquired brain injury (sABI). VErticalization by tilt table equipped with robotic-assisted lower limbs cyclic Mobilization (VEM) may facilitate a safer adaptation to vertical posture, reducing orthostatic hypotension occurrence. This multicenter randomized controlled trial (RCT) aims at investigating efficacy, safety, and usability of VEM compared to Traditional Verticalization (TV) using a conventional tilt table in cognitive-motor rehabilitation of sABI patients; **Methods**: a total of 118 sABI patients with or emerged from prolonged Disorder of Consciousness (pDoC and eDoC) will be enrolled in six post-acute Neurorehabilitation Units and randomly allocated to VEM or TV arm (for each arm: total 25 sessions of 30 min daily treatment/5 days/week/5 weeks). Patients will undergo clinical–functional assessment, resting EEG recording and blood sampling, before, at the end of treatment, and after 1 month; **Results**: we will expect possible differences in safety and usability of verticalization between VEM and TV rehabilitative intervention and in their efficacy to improve clinical–functional findings and brain indices; **Conclusions**: this RCT will provide new insights for the intensive, tailored and safe neurorehabilitation intervention in patients with sABI.

## 1. Introduction

Survivors from a severe Acquired Brain Injury (sABI; i.e., severe traumatic or non-traumatic brain injury leading to a comatose state with a Glasgow Coma Scale ≤ 8 for at least 24 h in the acute phase) can persist in a clinical condition of prolonged Disorder of Consciousness (pDoC; i.e., patients in vegetative state/unresponsive wakefulness syndrome, VS/UWS, or in minimally conscious state, MCS) or emerge from DoC (eDoC) with a moderate or severe cognitive motor disability [1]. Both American and Italian guidelines recommended an early post-acute admission of such complex disabled individuals in specialized rehabilitation units with high expertise in multidisciplinary care and multimodal diagnosis and prognosis [1,2]. These dedicated settings provide a comprehensive rehabilitation program that includes medical stabilization, alternate positioning, motor and cognitive training and speech therapy, to prevent and treat clinical complications (e.g., contractures, spasticity, and heterotopic ossifications) and to facilitate recovery of cognitive-motor and functional abilities.

In the rehabilitation phase, the early recovery of the upright position (i.e., verticalization) is crucial to prevent secondary complications due to immobility (e.g., stasis pneumonias, deep vein thrombosis, pressure ulcers) [3], enable the stabilization of the hemodynamic balance [4], promote the cognitive performance improvement (especially vigilance and attention) [5], and to ameliorate the muscular-cutaneous trophism and the control of trunk and limbs. However, the Traditional Verticalization (TV) using a conventional tilt table can be hampered by orthostatic hypotension due to cardiac output reduction because of blood pooling in the lower extremities and/or co-existing central sympathetic system impairment [6]. Since its introduction by Czell in 2004 [7] the tilt table equipped with robotic-assisted lower limbs cyclic mobilization has been proposed as a safe and suitable device for a controlled verticalization to facilitate the adaptation to vertical posture in bedridden patients with brain-injury since the acute phase [8]. A combined assisted lower limbs mobilization can activate the musculo-venous pump that enhances counter gradient venous blood flow return to the right heart from systemic circulation, thus resulting in better cardiac output and lower side effects (e.g., orthostatic hypotension) occurrence [9,10]. However, despite the potential benefits and growing popularity of robot-based rehabilitation [11], no conclusive data on cognitive-motor effects of controlled verticalization in patients with sABI have been found, likely because of the methodological bias of the available clinical trials (e.g., small or heterogeneous cohorts ranging from acute to chronic patients, absence of clear randomization; lack of blinding in outcome assessors [5,8,12,13,14]. To minimize bias due to confounding, the present randomized controlled trial (VEM-sABI) will compare multiple clinical, neurophysiological, and biological effects of combined robot-assisted VErticalization and lower limbs Mobilization (VEM) versus a TV in a large cohort of patients with sABI admitted to multiple post-acute rehabilitation settings. The primary aim of the VEM-sABI study will be to evaluate the efficacy of VEM versus TV in promoting short-term recovery of cognitive functioning in a large cohort of patients with sABI. Secondary aims will be to evaluate VEM vs. TV in: (i) preventing or reducing spasticity; (ii) promoting lower limb movements; (iii) reducing functional disability; (iv) and an additional secondary aim will be to evaluate the usability and safety of the two devices from the professional’s point of view. Exploratory aims will be to evaluate the efficacy of VEM vs. TV in: (i) promoting the recovery of consciousness in patients with pDoC; (ii) preventing clinical complications; (iii) maintaining the possible improvement in clinical–functional measures at 1 month after treatment. Additionally, it is crucial to also investigate the patients’ physiological features (such as neurophysiological indices of brain activity and biomarkers of brain damage and plasticity) to accurately outline patients with higher probability to respond to the treatment and detect sub-clinical outcomes [15]. In this context, additional exploratory objectives of study will be to evaluate the effect of VEM vs. TV on brain functionality and neuronal plasticity.

## 2. Materials and Methods

### 2.1. Trial Design and Participating Centers

This is a non-commercial, non-profit clinical investigation conducted under the “Fit for Medical Robotics” initiative, funded by the Italian Ministry of University and Research via the National Complementary Plan to the National Recovery and Resilience Plan, Investment I.1 (Call D.D. 931/2022).

This multicenter study is a single-blinded, randomized controlled trial (RCT), with two treatment-arms (1:1; VEM and TV), enrolling patients with sABI admitted to 6 Italian post-acute neurorehabilitation units (see Acknowledgments). The neurorehabilitation units were selected for their high expertise in the care of patients with sABI. Two additional expert laboratories will analyze blood biomarkers and will build and manage the electronic database and run a quantitative analysis of EEG (see Acknowledgments for the contributors of participating centers). The study protocol has been elaborated according to the Standard Protocol Items: Recommendations for Interventional Trials (SPIRIT; see Table 1) [16,17] and the Template for Intervention Description and Replication (TIDieR) checklist (see Supplementary Materials). The study was registered at ClinicalTrials.gov (ID: NCT06469983) on 14 June 2024.

### 2.2. Study Population

All patients with sABI consecutively admitted to the participating centers who meet the inclusion and exclusion criteria reported in Table 2 will be enrolled. Eligible conscious patients or legal representative/primary caregiver of pDoC patients will be orally informed about the rationale, aims, and procedures of the study in order to obtain their written informed consent. Purposes, procedures, and time points of the study will be clearly explained after a semi-formalized interview, whose structure is shared across centers, to either the eligible patients (if the Level of Cognitive Functioning, LCF, is between 7 and 8) or the patient’s legal representative/primary caregiver (if the assessment of cognitive functioning suggests that the patient may not understand all the information, e.g., for patients with LCF between 2 and 6). In the latter case, if a patient were to reach a higher LCF during treatment, she/he would be personally asked to sign an informed consent form.

#### Sample Size

Sample size was estimated based on information from a previous study [18] enrolling patients with MCS allocated to advanced robotic verticalization using the Erigo^®^ (Hocoma, Volketswil, Switzerland) device or traditional verticalization with a traditional tilt table. The comparison of the LCF score between the two groups after eight weeks of treatment led to an increase from 3.13 ± 1.41 to 3.60 ± 1.50 in the control group (n = 15) and from 3.60 ± 1.05 to 4.40 ± 1.06 in the experimental group (n = 15; effect size f = 0.248). For a two-sided α of 0.05 and a power of 80%, we will estimate enrolling at least 49 subjects per arm (VEM and TV). To account for a possible dropout rate of 20%, a total of 118 patients will be enrolled (59 subjects per arm).

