Age between 18 and 75 years; sABI due to traumatic, vascular, anoxic, or mixed etiology; Stable behavioral/cognitive diagnosis on at least 4 behavioral evaluations in 1 week using the Italian version of the CRS-R in patients with pDoC, or the LCF-based cognitive assessment in patients with eDoC; Time post-injury between 28 days and 6 months [1]; Not recovered upright station; Written informed consent by the patient’s legal representative/primary caregiver.	Severe medical conditions hampering verticalization (e.g., severe hypotension or conditions realizing hemodynamic instability, end stage or severe symptomatic heart failure with reduced ejection fraction, cardiac arrhythmia of new diagnosis or arrhythmic flare, severe hepatic failure, chronic severe lower limb arterio-venous disease, sepsis/septic shock, thrombus venous embolism of new diagnosis, severe autonomic dysreflexia); Severe medical conditions hampering lower limb mobilization (e.g., fractures, heterotopic ossifications); Severe medical conditions impacting EEG activity (e.g., sub-continuous or abundant EEG epileptiform abnormalities); Severe medical conditions influencing consciousness/cognitive status, such as severe hyponatremia or hypoglycemia; Contraindications to the use of Erigo^®^Basic and/or Erigo^®^Pro (Hocoma, Volketswil, Switzerland) as per technical data sheet (see Appendix A); Presence of prohibited drugs (see Appendix B).

Abbreviations: CRS-R = Coma Recovery Scale-Revised; eDoC = emergence from Disorder of Consciousness; EEG = electroencephalography; LCF = Level of Cognitive Functioning; pDoC = prolonged Disorder of Consciousness; sABI = severe Acquired Brain Injury.

**Table 3 jcm-14-06628-t003:** Summary of primary, secondary, and exploratory outcomes and measures.

Outcome	Timing, Measure
Primary outcome: Global cognitive functioning	At T0 and T1: LCF
Secondary outcomes:	
Functional disability Spasticity of lower limbs Muscular strength of lower limbs Functional independence Usability of devices from physiotherapists Adverse events	At T0, T1 and T2: DRS At T0, T1 and at T2: MAS At T0, T1 and T2: MRC. Additional clinical observation of spontaneous or reflex movement to pain stimulation in pDoC patients At T0, T1 and T2: mBI At T1: SUS Each daily session: AER
Exploratory outcomes:	

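### The stated 80% power rests on an effect size that best fits an average over baseline and post-treatment; for the planned baseline-adjusted T1 comparison, power at 49 per arm is probably below 80%

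*Protocol article*

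**What the plan says.** The Sample Size section of the protocol article introduces its source data as "The comparison of the LCF score between the two groups after eight weeks of treatment". The control arm is reported as "an increase from 3.13 ± 1.41 to 3.60 ± 1.50 in the control group (n = 15") and the other arm as "from 3.60 ± 1.05 to 4.40 ± 1.06 in the experimental group (n = 15; effect size f = 0.248"). It continues "For a two-sided α of 0.05 and a power of 80" per cent, "we will estimate enrolling at least 49 subjects per arm (VEM and TV"), and then "To account for a possible dropout rate of 20%, a total of 118 patients will be enrolled (59 subjects per arm").

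The section does not say which test was used, which contrast f describes, how many measurements enter it, or what correlation was assumed between them.

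On the analysis side, Table 3 gives the primary outcome as "At T0 and T1: LCF". Section 2.6 adjusts every model for the baseline value of the outcome. Allocation is randomised, "with two treatment-arms (1:1; VEM and TV").

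**The concern.** Randomisation makes the expected baseline difference zero, and the planned model adjusts for whatever difference arises by chance. An effect size that includes a pre-treatment gap therefore does not describe anything the primary analysis estimates. In the source study the arms already differed by 3.60 − 3.13 = 0.47 points at baseline, which is large beside the 0.33 points by which their changes differed.

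If f = 0.248 absorbs part of that gap, the 80% belongs to a different comparison from the one the trial will make. Readers will rely on that figure when they interpret the result, most of all if the primary comparison is not significant.

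**Working it through.** **Inputs, all from Sample Size.** LCF in the control arm 3.13 (SD 1.41) to 3.60 (SD 1.50); in the experimental arm 3.60 (SD 1.05) to 4.40 (SD 1.06); f = 0.248; two-sided α 0.05; 80% power; 49 per arm. The baseline–T1 correlation ρ is not given, so it is varied from 0.5 to 0.9 as an assumption.

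**1. Reproducing f.**
- Time-averaged means: (3.60 + 4.40)/2 = 4.000 and (3.13 + 3.60)/2 = 3.365; difference 0.635.
- Pooled SD: √[(1.41² + 1.50² + 1.05² + 1.06²)/4] = 1.271.
- f = (0.635/2)/1.271 = 0.250, against 0.248 stated.
- T1 alone: SD √[(1.50² + 1.06²)/2] = 1.299, so f = 0.40/1.299 = 0.308.
- Baseline alone: SD √[(1.41² + 1.05²)/2] = 1.243, so f = 0.235/1.243 = 0.189. The mean of 0.189 and 0.308 is 0.2485.
- Difference in change: 0.80 − 0.47 = 0.33. With ρ = 0.5 the SD of change is 1.272, so f = 0.165/1.272 = 0.13.

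The averaged contrast is the closest fit. Its 0.635 is (0.47 + 0.80)/2, so the baseline gap enters with the same weight as the T1 difference.

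**2. Reproducing 49 per arm.**
- Between-group test over two measurements: λ = N f² × 2/(1 + ρ). With ρ = 0.5 and N = 98, λ = 98 × 0.0615 × 1.333 = 8.04, power 0.801. N = 96 gives 0.793. So 98, or 49 per arm, is matched exactly.
- T1 ANCOVA with f on the unadjusted SD: λ = N f²/(1 − ρ²). At ρ = 0.5, 1/(1 − 0.25) = 1.333, the same multiplier, so this also gives 98. It implies a T1 difference of 2 × 0.248 × 1.299 = 0.64 points.
- Plain two-group test at d = 2 × 0.248 = 0.496: 49 per arm gives 68% power; 65 per arm are needed by the t test.

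**3. Power at 49 per arm for the baseline-adjusted T1 contrast.** Residual SD = 1.299 × √(1 − ρ²). The source's adjusted difference is 0.80 − b × 0.47, with b = ρ × 1.299/1.243. Power comes from the noncentral t with noncentrality (difference/residual SD) × √(49/2).

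| ρ | Residual SD | Adjusted difference | Power, adjusted difference | Power, 0.33 points |
|---|---|---|---|---|
| 0.5 | 1.125 | 0.55 | 68% | 30% |
| 0.7 | 0.928 | 0.46 | 67% | 41% |
| 0.8 | 0.779 | 0.41 | 73% | 55% |
| 0.85 | 0.684 | 0.38 | 78% | 66% |
| 0.9 | 0.566 | 0.36 | 87% | 81% |

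The raw T1 difference of 0.80, unadjusted with SD 1.299, gives 86%, but it still contains the baseline gap.

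**The case against.** The test is unnamed, so the averaged contrast is an inference. A reader might infer that 49 can come from no other calculation. The documents do not support that: a T1 ANCOVA at ρ = 0.5 gives the same 98, and Section 2.6 does describe an ANCOVA framework. On that reading the design has 80% power for a baseline-adjusted T1 contrast at the f assumed. The difference in change could also produce f near 0.248, at ρ of about 0.86 (f is 0.236 at 0.85 and 0.289 at 0.9), with no baseline gap counted.

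These alternatives stand as possibilities, but neither explains the paragraph. The ANCOVA reading needs a T1 difference of about 0.64 points, and the cited data offer 0.80 raw, about 0.55 adjusted at ρ = 0.5, or 0.33 in change. The change-score reading gives an f but not 49 without a further assumption.

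A reader might also infer that power is only 25–30%. That takes 0.33 points as the target and ρ = 0.5. The protocol never names 0.33 as its target. For an analysis that adjusts for baseline, the source's adjusted difference is the more relevant figure, and its shortfall is much milder.

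Finally, LCF has eight levels and Section 2.6 plans cumulative-logit mixed models for ordinal outcomes. The power figures here are normal-theory approximations to that analysis. This limits their precision.

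**Conclusion.** The point holds in a limited form. The protocol's own inputs do not support the stated 80% for its baseline-adjusted T1 comparison. The best-fitting derivation counts the source study's 0.47-point baseline gap as effect, and the one alternative found that also gives 98 at the stated two-sided α rests on a difference the cited data do not contain.

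Power at 49 per arm is probably below 80%: about 67–78% for the source's adjusted difference and about 30–66% for 0.33 points, over ρ 0.5–0.85. It reaches 80% as ρ nears 0.9. All of this depends on an unstated correlation, on SDs from 15 patients per arm, and on the normal approximation.

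Confidence is medium because the calculation behind f is not shown. The paragraph should be corrected. It does not follow that the trial must be enlarged or that its analysis is wrong.

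**What to change.** Rewrite the sample-size paragraph for the baseline-adjusted T1 contrast:
- Name the contrast, the assumed SD of LCF and the assumed baseline–T1 correlation.
- Drop the f that averages over baseline.
- Keep the planned size, and report power and the smallest detectable LCF difference over a range of correlations.
- Say that these are approximations to the ordinal mixed model.

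For the detectable difference, 59 per arm with 20% loss leaves 59 × 0.8 = 47 evaluable. The 80% power point is then about 0.58 residual SDs. With SD 1.30 this is about 0.66, 0.54, 0.46 or 0.33 points at ρ 0.5, 0.7, 0.8 or 0.9.

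The cost is one paragraph and a less favourable power statement. Enrolment, design and analysis stay as they are.

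### Enrolling 118 does not cover a 20% dropout: 59 per arm leaves 47, below the 49 that the plan requires

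*Protocol article*

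**What the plan says.** The Sample Size section (under 2.2, Study Population) takes LCF results from an earlier study with 15 patients per group, expressed as "effect size f = 0.248". At a two-sided α of 0.05 and 80% power it concludes: "we will estimate enrolling at least 49 subjects per arm (VEM and TV"). The allowance for losses follows directly: "To account for a possible dropout rate of 20%, a total of 118 patients will be enrolled (59 subjects per arm"). The formula behind the allowance is not printed. The Abstract repeats the enrolment figure as "a total of 118 sABI patients".

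**The concern.** A dropout rate is a fraction of the patients enrolled. A plan that enrols 59 per arm to allow for a 20% loss is therefore saying that 80% of 59 is at least 49, and it is not. The likely cause is a common slip: adding 20% to the required number instead of dividing that number by the expected completion fraction.

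The plan's statement that its enrolment meets its own target is at stake. If dropout reaches the planned rate, the trial ends below the number that it calls a minimum and below its 80% power, even if the effect size is accepted in full. Section 2.6 (Statistical Plan) lists many ways for a patient to leave treatment: a change in a proscribed drug, a severe adverse event, transfer to an acute ward, futility, missed sessions and withdrawal. The Discussion expects dropouts too. The rate that the trial can tolerate should therefore be stated correctly.

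**Working it through.** **Inputs, all from the Sample Size section.** Required number 49 per arm (98 in total); dropout 20%; enrolment 59 per arm (118 in total); α 0.05 two-sided; power 80%; f = 0.248.

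**1. Reproducing the plan's enrolment.**
- Required n × (1 + dropout): 49 × 1.2 = 58.8, rounded up to 59.
- In total: 98 × 1.2 = 117.6, rounded up to 118.

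Both match the printed figures. That the plan multiplied by 1.2 is an inference, since no formula is given. The shortfall in step 2 does not depend on it.

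**2. What 118 delivers at 20% dropout.**
- Per arm: 59 × 0.8 = 47.2, about 47, against 49.
- In total: 118 × 0.8 = 94.4, about 94, against 98.

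**3. What 49 completers require.**
- Required n / (1 − dropout): 49 / 0.8 = 61.25, so 62 per arm and 124 in total, 6 more than planned.
- Rounding does not explain the gap: 60 × 0.8 = 48.0 and 61 × 0.8 = 48.8 also fall short. The first size that suffices is 62 (62 × 0.8 = 49.6).

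**4. Dropout that 118 tolerates.** 1 − 49/59 = 10/59 = 16.9%.

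**5. Effect on power.** The section names no test, number of measurements or correlation, so these have to be assumed. A repeated-measures ANOVA, between-group F test, with two measurements (m = 2) and correlation ρ = 0.5 gives N = 98, which is the plan's 49 per arm. Its noncentrality is λ = f² × N × m / (1 + (m − 1)ρ).
- N = 98: λ = 0.0615 × 98 × 2 / 1.5 = 8.04; power 80.1%.
- N = 94: λ = 0.0615 × 94 × 2 / 1.5 = 7.71; power 78.4%.

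The loss is about 1.7 points. It hardly depends on the assumed test. By the normal approximation, any test with 80% power at 98 has a standardised effect of 1.960 + 0.842 = 2.802. At 94 this becomes 2.802 × √(94/98) = 2.744, and 2.744 − 1.960 = 0.784, a power of about 78%.

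**The case against.** The strongest reply is that dropouts are not simply lost. Section 2.6 says that patients who violate the protocol leave treatment but remain in the analysis through their last clinical observation, under intention to treat and a mixed model assuming data missing at random. Most routes to dropout are listed there as violations. On that reading, 47 per arm counts completers, not the analysis set. This is fair as far as it goes, and completers is the better word. It does not rescue the sum. The Sample Size section inflates precisely because it treats dropouts as lost to the 49; if they counted in full, no inflation would be needed. Table 3 places the primary outcome, LCF, at T0 and T1 only, so a patient lost before T1 has no post-treatment primary value. Carrying an earlier value forward does not create one.

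The second reply is that the matter is too small to raise. The gap is two patients per arm, the 20% is only a possible rate, and an effect size taken from 15 patients per group is far more uncertain than 1.7 points of power. The size is indeed small, and it changes no design feature or analysis. It is nevertheless a checkable error in the sample size for the primary outcome, and it costs almost nothing to correct.

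The third reply is that the 78.4% is not the plan's own figure. That is correct: it comes from a reconstruction with an assumed design. The shortfall of 47 against 49 needs no such assumption.

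**Conclusion.** The concern holds; the statement is wrong as written. On the plan's own figures, 118 enrolled with 20% dropout gives about 94 completers (47 per arm), not the 98 (49 per arm) required. The enrolment supports a dropout of 16.9%. Nothing elsewhere in the article corrects this.

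The consequence is modest: about 2 completers per arm and about 1.7 points of power (80.1% to 78.4%). The power figures assume two measurements with correlation 0.5. The head-count shortfall rests only on printed numbers and on reading the dropout rate as a share of those enrolled. The mixed model may soften the practical loss but does not make the sentence true. Whether 49 per arm is itself well founded is a separate question, and this conclusion does not depend on it.

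**What to change.** Correct the last sentence of the Sample Size section in one of two ways:

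- Keep 118 and 20%, and state the yield: with 118 enrolled and 20% dropout, about 94 patients (47 per arm) complete. Give the power at 94, about 78%, and name the test, number of measurements and correlation on which it rests.
- Keep 118 and 49 per arm, and state that this enrolment allows for about 17% dropout.

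Either costs one sentence and a slightly less favourable figure, with no extra patients, and the 118 in the Abstract stays as it is. The first option corrects the description but leaves the trial slightly under 80% power at 20% dropout, and the text should say so. If the sponsor wants to keep both 49 per arm and a 20% allowance, the matching enrolment is 124 (62 per arm). That is 6 more patients, and the Abstract would then need to change as well.
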